## 10.2. Source data and documents

Source data is all the information contained in original documents, or in authenticated copies of these documents, which relate to clinical examinations, observations or other activities carried out as part of research involving the person human and which are necessary for the reconstruction and evaluation of research. The documents in which the source data are recorded are called source documents, regardless of the medium used (paper, electronic, etc.).

The data a) are collected on a specially dedicated computer database and are shared by all the PrevHPV

SC teams. These data are public data, accessible via online statistics. They will be verified with the principals/directors of the middle schools.

Data b) are collected on a specially dedicated computer database and are shared between team 2 and team 3. They will be collected by teams 2 and 3 by interviewing the GPs participating in the training.

Data c): (i) SNDS data (for participating municipalities: reimbursement of a HPV vaccine for a young person aged 11 to 14, by sex, and prescribing health professional) will be made available to team 8 (dedicated data access portal) after contracting with the CNAM and obtaining authorizations. (ii) data from family planning and education centers, vaccination centers and number of vaccines used for research will be collected by teams 1, 3, 4, and 5 for each geographical area that each team is in charge of and will be transmitted to team 8 for the analysis of the main objective and to team 6 for the evaluation of efficiency.

Data d) are collected via the KAPB-6C self-questionnaires administered online to the different target populations on a database generated by team 7.

Data e) are collected via self-questionnaires administered online to SeSa students on a database generated by team 5.

Data f) on satisfaction with the interventions are collected via online or paper self-questionnaires. (SeSa students, middle school professionals, adolescents and parents will be managed by teams 4 and 5; GPs by team 2).

Data g) and h) are collected as the intervention components are designed and implemented by the SC project teams on an electronic CRF and will be transmitted to team 1 for data g) and to team 6 for data h). The online self-administered questionnaires (KABP-6C) will be developed using RedCap® software. The data will be stored with the inclusion number but without other identifying information in the RedCap® collection databases, which will allow an anonymous survey to be carried out. After closure, the data from each survey will be extracted into a database and deleted from the RedCap® software.

### 10.3. Data circuit

| Data | Source                             | Team(s) in charge of recovering data | Team(s) to whom the data is transmitted (or accessible) for analysis |
|------|------------------------------------|--------------------------------------|----------------------------------------------------------------------|
| a)   | Public data                        | 1                                    | All SC teams                                                         |
| b)   | Interviewing GPs                   | 2 and 3                              | 2                                                                    |
| c)   | SNDS
Other than SNDS            | 8
1, 2, 3, 4, 5                   | 8 and 6 (efficiency)                                                 |
| d)   | Online self-questionnaires         | 7                                    | 7                                                                    |
| e)   | Online self-questionnaires         | 5                                    | 5                                                                    |
| f)   | Online self-questionnaires         | 2, 4, 5                              | 2, 4, 5                                                              |
| g)   | Interviewing project teams on site | 1, 2, 3, 4, 5                        | 1                                                                    |
| h)   | Interviewing project teams         | 1, 2, 3, 4, 5                        | 6                                                                    |

Each type of data, a) to h) above, will be hosted on computers of the teams to whom the data is transmitted for analysis. They will be accessible to members of the the PrevHPV SC according to the rules of the consortium.

The data collected cannot be transmitted to third parties outside the 8 PrevHPV SC teams.

The data management, the statistical analysis plan, the database freezing and the regular backup of the data will be carried out according to the procedures in force within each team which is in charge of the statistical analysis for the part which concerns it.

### 10.4. Conservation of research documents

Documents relating to research are archived in accordance with current regulations.

The sponsor and the PrevHPV SC keep the documents relating to the research, which are specific to them until the end of the statistical analyzes (expected duration: 5 years after the freezing of the database) making it possible to meet the objectives of the research (conservation of the active base), then beyond for a total period of 15 years (conservation in archiving).

No movement or destruction can be done without the agreement of the sponsor. At the end of the regulatory archiving period, the sponsor will be consulted for destruction.

All data, documents and reports are subject to audit or inspection.

## 11. STATISTICAL ANALYSIS

### 11.1. Responsible for statistical analysis

Responsible for the analysis relating to the primary objective and secondary objective 2 (evaluation of effectiveness): [name] (Team 8)

Responsible for the analysis relating to secondary objective 1 (assessment of knowledge, attitudes and practices, antecedents of vaccine hesitancy, KABP-6C): [name] (Team 7)

Responsible for the analysis relating to secondary objectives 3 and 4 (evaluation of efficiency and budgetary impact): [name] (Team 6)

Responsible for the analysis relating to secondary objective 5 (evaluation of the implementation):  
[name] (Team 1)

## **11.2. Sample size calculation**

The sample size will depend on the number of participating middle schools, which is not known at this stage. This is why at this stage, we will consider the situation of a single middle school per municipality. The calculation below is therefore conservative.

According to government statistics, the number of students per middle school is on average 466. Assuming one middle school per cluster, the average size of the cluster would therefore be 466 adolescents aged 11 to 14. Twenty percent of middle schools having fewer than 300 students and 13% having more than 700, we retain a coefficient of variation of 0.5 in the size of the clusters.

The intra-class correlation coefficient is set at 0.05.

The current prevalence of initiation of vaccination from 11 to 14 years old is 16.1% among girls and 0% among boys due to the date of application of the HAS recommendation on the vaccination of boys. Girls representing 48.85% of the population in this age group, the prevalence among 11-14 year olds is 7.86%. The objective of the intervention is to increase this prevalence by at least 10% (based on data published in the literature). Considering two groups, we would need 15 clusters per group to reach a power of 90% and considering an alpha risk of 5%.

This research will include 6 groups, and the analysis will be carried out using a modeling approach in which several parameters will be tested: effects of interventions, and potential interactions between interventions. It is not planned to make multiple 2 to 2 comparisons. Therefore the alpha risk has not been corrected.

In the end, knowing that 6 groups will be formed, we plan to include a total of 90 municipalities (15 per group). This corresponds to an expected sample of 41,940 adolescents aged 11 to 14, under the assumption of a single middle school per municipality.

## **11.3. Description of the statistical analysis plan**

A data management and statistical analysis plan will be drawn up by the PrevHPV SC before the start of the research.

Qualitative variables are expressed as counts and percentages, and quantitative variables as means, standard deviations, medians and interquartile ranges.

All analyzes are carried out on an intention-to-treat basis. No interim analysis (effectiveness or futility) is planned before the end of the intervention.

### **11.3.1. Analysis of the primary outcome**

The prevalence of vaccination (at least 1 dose received and complete vaccination) among adolescents aged 11-14 is calculated (from SNDS data, supplemented where appropriate with data from vaccination centers, family planning centers and vaccines delivered in middle school) at the different measurement times (before intervention, 2 months, 6 months and 12 months after intervention) and in each of the six study groups. A calculation of this prevalence according to the sex and deprivation level of the municipality of residence of the adolescents is also planned.

Concerning the analysis of the primary outcome (vaccination coverage rate), an analysis at the cluster level will be carried out, that is to say that the unit of analysis will be the municipality and not the adolescent who is nested in his or her municipality. The data will be collected at the municipality level. Each municipality (= cluster) will be weighted by its size. A modeling approach will be used, carrying out a global analysis of the 90 randomization units. The model will be a linear model in which we will consider 3 fixed effects (one per component) and potential interactions between component. The baseline VC will be considered as an adjustment variable.

The evolution of the VC over time (M2, M6, M12) will also be modeled by considering a longitudinal model, and adjusting for the baseline VC rate.

Subgroup analyzes will be carried out according to sex, deprivation level (FDep) and considering a modeling approach with interaction terms.

Depending on the quality of the data reported by vaccination centers and family planning centers, sensitivity analyzes will be carried out to take into account only SNDS data and the number of vaccines delivered in middle school.

The analyzes are carried out using SAS software version 9.4 or later (SAS Institute Inc.) or R, and considering two-sided statistical tests and a level of significance of 5%.

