### 5.2. Inclusion and non-inclusion criteria

Inclusion in PrevHPV research is carried out at 2 levels:

- (i) the inclusion of participating municipalities,
- (ii) the inclusion of people participating in the research.

- **Inclusion of participating municipalities:**

The inclusion criteria for municipalities are as follows:

- Municipalities of the academies Aix-Marseille, Clermont-Ferrand, Créteil, Grenoble, Lille, Limoges, Lyon, Nancy-Metz, Nantes, Reims, Strasbourg, Toulouse, Orléans-Tours, Versailles,
- Municipalities in which a total of 1 to 4 middle schools (public or private) are located,

- Municipalities drawn at random from the group of 409 municipalities to be requested to participate in the research,
- Municipalities where all middle schools agree to participate in research.

- **Inclusion of people participating in interventions:**

Inclusion criteria

- ✓ For the intervention component 'Training of GPs' are:

- GPs practicing in the municipalities randomized to groups 1, 2, 5,
- Agreeing to participate in training in motivational interviewing and the use of the decision-aid tool.

**Will not be included:** (i) GPs having exclusively a Particular Mode of Practice, (ii) whose practice within the municipality is planned to stop during the first half of 2021, (iii) GPs with no internet access.

- ✓ For the intervention component 'Education, Motivation, Mobilization', are:

- Adolescents (girls and boys), enrolled in Grades 8 & 9 classes in middle schools (public and private) located in the municipalities randomized to groups 1, 2, 3 and 4,
- Parents of adolescents (girls and boys), enrolled in Grades 6 to 9 classes in middle schools (public and private) located in the municipalities randomized to groups 1, 2, 3 and 4, who agree to participate in an information/education session,

- ✓ For the intervention component 'Facilitation of access to vaccination', are:

- Adolescents (girls and boys), enrolled in middle schools (public and private) located in municipalities randomized to groups 1 and 3, in Grades 6 to 9 classes,
- Aged 11 to 14 on the date of injection, with possible catch-up among 15-19 year olds for those who have repeated a grade, in accordance with the recommendations,
- Not vaccinated against HPV on the date of offer of vaccination in middle school (April - May 2021),
- Whose parents (or representatives of parental authority) agree to the initiation of HPV vaccination in middle school,

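### The primary model weights municipalities by size but names no variance to match; with ordinary model-based standard errors the nominal 5% test would run at about 7 to 11%

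*Protocol*

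**What the plan says.** Section 11.3.1 of the protocol makes the municipality the unit of analysis. One linear model is fitted to all 90, with an effect for each of the three components, possible interactions, and baseline coverage as a covariate. On weights it says: "Each municipality (= cluster) will be weighted by its size". Inference is made "considering two-sided statistical tests and a level of significance of 5" per cent. The section does not say how standard errors are to be obtained.

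Section 11.2 sizes the trial with an ICC of 0.05 and a mean of 466 adolescents per cluster, one middle school per municipality being assumed. On size variation: "we retain a coefficient of variation of 0.5 in the size of the clusters". On the single-school assumption: "The calculation below is therefore conservative". The result is "we would need 15 clusters per group to reach a power of 90% and considering an alpha risk of 5" per cent.

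The eligibility rule in 5.2 is wider than that assumption: "Municipalities in which a total of 1 to 4 middle schools (public or private) are located". Section 3.1 defines the outcome as vaccinated adolescents aged 11 to 14 divided by all adolescents of that age.

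**The concern.** A linear model with size weights treats the variance of each municipality's coverage as proportional to 1/size. That would be right if adolescents within a municipality were independent. Section 11.2 says that they are not, and at its ICC nearly all the variance lies between municipalities, where size makes no difference. Large municipalities then carry more weight than their precision justifies. This is harmless to the estimate, but the usual weighted-least-squares standard error takes the weights at face value and comes out too small.

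At stake are the level of the primary tests and the width of their confidence intervals. Section 11.2 also makes no alpha correction for the several effects to be tested, so there is no slack to absorb an inflated error.

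**Working it through.** **Inputs.** From 11.2: ICC ρ = 0.05, mean size m = 466, CV = 0.5, 15 clusters per group, 90% power, and "the prevalence among 11-14 year olds is 7.86" per cent. The target is "The objective of the intervention is to increase this prevalence by at least 10" per cent, read here as percentage points (a relative 10% would need about 1,660 clusters per group). Two-sided 5% is from 11.3.1.

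**1. Reproducing the plan's figure.** Unclustered size per arm: (1.960 + 1.282)² × (0.0786 × 0.9214 + 0.1786 × 0.8214) / 0.10² = 230.2. Design effect with unequal clusters: 1 + ((1 + 0.5²) × 466 − 1) × 0.05 = 30.075. Clusters per group: 230.2 × 30.075 / 466 = 14.86, so 15. Without the CV term the design effect is 24.25 and about 12 clusters suffice. The plan's 15 therefore includes the penalty for unequal sizes.

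**2. How variance depends on size.** A municipality of size n has coverage variance proportional to ρ + (1 − ρ)/n. At n = 466 this is 0.05 + 0.95/466 = 0.05204, of which 0.05/0.05204 = 96% is free of n. Doubling n to 932 gives 0.05102, a fall of 2%. Size weights assume a fall of 50%.

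**3. True against model-based variance of a size-weighted arm mean (per cluster).**
- True: ρ(1 + CV²) + (1 − ρ)/m = 0.0625 + 0.00204 = 0.06454.
- Model-based: ρ + (1 − ρ)/m = 0.05204.
- Ratio: 1.240, so the true standard error is 1.11 times the printed one, and the printed one is 1 − 1/1.11 = 10% too small.
- Type I error: 2 × (1 − Φ(1.960/1.114)) = 7.8%.

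The two variances equal 30.075/466 and 24.25/466. The default standard error thus drops the CV term that 11.2 included.

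**4. Mixed numbers of schools.** The documents give no split. Assuming 60/25/10/5% of municipalities with 1/2/3/4 schools and independent school sizes with CV 0.5, mean size is 746 and CV 0.67. True variance 0.0735, model-based 0.0513, standard error ratio 1.20, printed standard error 17% too small, type I error 10.2%.

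**5. Simulation under no effect.** Six arms of 15, beta-binomial outcomes, gamma-distributed school sizes, 6,000 runs per setting. Ranges are over the three component effects; rows without the baseline covariate cover models with and without interactions.

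| Setting | Model-based | HC3 |
|---|---|---|
| ICC 0.05, CV 0.5, no baseline covariate | 7.4–8.0% | 4.3–4.8% |
| ICC 0.05, CV 0.5, baseline correlation 0.7 or 0.9 | 6.9–7.9% | 4.3–4.9% |
| ICC 0.05, CV 0.67, no baseline covariate | 9.7–11.0% | 4.3–5.7% |
| ICC 0.05, CV 0.67, baseline correlation 0.7 | 9.0–9.9% | 4.0–4.8% |
| ICC 0.01, CV 0.5, baseline correlation 0.7 | 6.5–6.9% | 4.2–4.5% |
| ICC 0.01, CV 0.67, baseline correlation 0.7 | 8.4–9.2% | 4.3–5.2% |

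Equal weights at ICC 0.05 give 4.4–5.4% with model-based standard errors.

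**6. The word *conservative*.** Two-arm power at 15 per group, size weights, assumed school mixes:

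| Schools per municipality | CV | Clusters needed | Power |
|---|---|---|---|
| One each (as planned) | 0.50 | 14.9 | 90.3% |
| Two each | 0.35 | 13.2 | 93.3% |
| 1/2/3/4 at 25% each | 0.55 | 15.1 | 89.7% |
| 40/30/20/10% | 0.61 | 16.1 | 87.9% |
| 60/25/10/5% | 0.67 | 16.9 | 86.3% |
| 70/20/7/3% | 0.67 | 17.1 | 86.0% |

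A larger mean size gains almost nothing at this ICC; a higher CV loses more.

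**The case against.** Four objections deserve an answer.

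- **The protocol does not say that model-based standard errors will be used.** This is correct: the inflation needs the weights and the default estimator together, and size weights with HC3 hold about 5%. A reader might infer that the weighting alone breaks the 5% level; the documents do not support that. But the protocol fixes the weights, the model and the level, and nothing in it points away from the default. A statistical analysis plan might settle the matter, but none is shown.
- **Size weights are the right choice for the outcome.** This stands. The prevalence in 3.1 is per adolescent, and so are the cost-effectiveness and budget questions. A reader might infer from the relative efficiency of 0.82 against optimal weights that information is wasted. That compares estimators of different targets, and the loss at CV 0.5 is already paid for in the 15 clusters.
- **Power for the components is not in doubt.** This also stands. A reader might take the 86 to 90% figures to mean that the stated 90% is too high for the component effects. In the additive model, education rests on about 30 against 30 municipalities and GP training on 45 against 45. With the same design effect, power for 10 points is 99.6% and over 99.9% at CV 0.5, and 99.0% and over 99.9% at CV 0.67. The lower figures apply to a 15 against 15 contrast.
- **The school mixes are assumed.** True. This limits the statement on 11.2 to unsupported: two schools everywhere would raise power.

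**Conclusion.** The point holds conditionally. If the size-weighted model of 11.3.1 is run with ordinary model-based standard errors, these are about 10% too small at the protocol's own ICC, mean size and CV, and the type I error is about 7 to 8%. With a CV of about 0.67 they are about 17% too small and the error is about 9 to 11%; that CV rests on an assumed split of schools and gamma-distributed school sizes. Baseline adjustment does not cure it (the correlations of 0.7 and 0.9 are assumptions), and a lower ICC of 0.01 reduces it only slightly.

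The claim in 11.2 that the calculation is conservative is unsupported, not shown to be false. It considers the mean cluster size and ignores the higher CV that a mix of one to four schools would bring.

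**What to change.** - **Section 11.3.1.** Keep the size weights and say that they target the adolescent-level prevalence of 3.1. State that tests and confidence intervals use an HC3 variance, or a permutation test that follows the stratified allocation actually used. Add near-equal inverse-variance weights, 1/(ICC + (1 − ICC)/n), as a sensitivity analysis, noting that they move the target towards the average municipality.
- **Section 11.2.** Delete the word *conservative*, or state that two-arm power is about 86% to 93% depending on how schools are distributed across municipalities.

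The cost is a line or two of code and wording. Printed standard errors become about 10 to 20% larger (ratios of 1.11 to 1.20), which is the honest width. The number of municipalities need not change.

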### **11.3.2. Analysis of secondary outcomes**

#### **(i) Analysis of secondary objective 1**

For the analysis of this objective, people with a positive change in intention/vaccination will be identified (change from “no” for both at T0 to “yes” for one of the two at T1).

The variables corresponding to the KABP-6C items will be created in particular by calculating knowledge scores and Likert scale medians.

For an analysis of T0, the percentages and medians of the items will be presented by intervention group, namely:

- a. By EMM groups 0 and 1, among participants without vaccination campaign, without taking into account the GP intervention
- b. By school interventions (campaign + EMM vs. without campaign or EMM), without taking into account the GP intervention
- c. By GP groups 0 and 1, among participants with EMM, without taking into account the vaccination campaign intervention

For an analysis of the main effects, the percentages of people with change and the medians of the differences will be presented by group (see a., b., and c.).

The differences will be tested first by suitable non-parametric tests (Fisher's and Wilcoxon, ranksum).

Multilevel models with a binary or continuous (linear) dependent variable will then be constructed in order to estimate the effect of interventions alone or in interaction, while taking into account intraclass correlation effects (cluster randomization). The interactions to be studied as a priority are:

- between the GP intervention and the school intervention (EMM+campaign),

- between the vaccination campaign intervention and the GP intervention (only possible in combination with EMM)
- between the EMM intervention and the GP intervention (only possible in the absence of a vaccination campaign)

For an analysis not taking into account individual evolution between T0 and T1, the effect of each intervention (alone or in interaction) will be estimated from a difference-in-difference model, i.e. including an interaction between the intervention group (among the 6 defined, with the control group as reference) and the temporal indicator “after” (vs. before) intervention.

Variations in the impact of intervention components will be explored by analyzes stratified by individual characteristics and KAP-6C (at T0). In order to test for significant differences between subgroups, we will examine 95% confidence intervals. In general, we will neither apply predefined statistical significance levels nor correct for multiple testing, but report exact P values. Interaction terms may be included in the models, if indicated.

Models including individual characteristics will be built for an analysis of the determinants of vaccination intentions.

Other analyzes will focus on the change from “intention without vaccination” to “vaccination declaration”; and on the association between individual characteristics, KAP-6C items at T0 or T0-T1 change.

Statistical analyzes will be carried out using STATA software.

